#### Blood and urine derived measures of cardiovascular risk

non-fasting blood and urine samples will be collected to assess established measures of cardiovascular risk, inflammation and vascular health, including glycosylated haemoglobin (HbA_1c_), lipids and lipoproteins (total cholesterol, high-density lipoprotein cholesterol, apolipoprotein A-1 and apolipoprotein B), high sensitivity C-reactive protein (hs-CRP), interleukin-6 (IL-6), asymmetric dimethylarginine (ADMA), and urine albumin to creatinine ratio.

Collected blood samples are centrifuged for 10 min at 1300 g within 30 minutes of collection. If unable to be centrifuged immediately, blood is stored in a fridge or on ice packs in a cool-box until centrifugation a maximum of 2-hours after collection. Following centrifugation, samples are transported on ice to be processed by Westerns Pathology, Darwin for lipids and HbA1c. Total cholesterol is assayed by enzymatic methods, and high-density lipoprotein cholesterol measured directly, with an ADVIA chemistry system (Siemens, Tarrytown, USA). HbA1c is determined by turbidimetric inhibition immunoassay with a COBAS INTEGRA (Roche Diagnostics, Indianapolis, USA). Other samples are stored at -80 degree Celsius. For samples collected in remote locations, storage for transportation is either on dry ice or in liquid nitrogen ("Biological Shipper", CryoPak Series, Taylor-Wharton, USA). Samples are stored for analysis at a later date for hs-CRP, IL-6, ADMA, apolipoproteins and glucose.

#### Self-administered questionnaires

Self-reported information pertaining to socio-demographic, oral health behaviours and general health factors is gathered at baseline, with the assistance of study personnel as required.

Socio-demographic details include age, sex, Aboriginal/Torres Strait Islander status, grandparental Indigenous status, education level, employment, English-as-first-language, house ownership, number of children, number of people who stayed in house the previous night and car ownership.

Oral health covariates include periodontal status and a self-report item pertaining to whether or not participants think they have gum disease.

General health covariates include behaviours such as smoking, current medication, current diagnoses (for diabetes etc), status of current diagnoses (controlled, uncontrolled etc) and stress (measured by the Kessler 10+ scale; a validated measure of distress that has been validated in a national health survey for Indigenous adults) [5].

### Primary and secondary outcomes

The primary outcome measures for purposes of this investigation will be carotid IMT and PWV. Secondary outcome measures will include CRP, IL-6, ADMA, and HbA1c.

### Sample size

Based on recent studies of Indigenous adults residing in the Northern Territory, we estimate that a sample size of 144 will provide 0.80 power to detect a 10 percent difference between groups in carotid IMT progression over 12-months, and a 10 percent reduction in PWV in the intervention group compared to the control group, at *P *< 0.05. The literature indicates that it is reasonable to expect effects of this magnitude following the periodontal intervention [25,26]. Allowing for an attrition rate of 45 percent over 12 months, 266 participants are required at baseline. In NSAOH, the proportion of Aboriginal adults with periodontal disease was estimated at 30 percent [10], however, it is likely that Aboriginal participants in NSAOH are not representative of the Aboriginal population in which we are interested. There are two main reasons: i) NSAOH participants were required to complete a telephone interview (ie to have an operating telephone and be registered in the electronic white pages); and ii) NSAOH participants were required to organise their own transport and to present for a scheduled dental examination at a local dental clinic. We posit that the NSAOH estimate is an under-estimation of periodontal disease prevalence in our target population, with anecdotal evidence suggesting that the prevalence is closer to 60 percent. We have estimated the prevalence of periodontal disease in our target population as 40 percent, meaning approximately 450 Indigenous adults will need to be screened in order to obtain 266 with moderate or severe periodontal disease.

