### Data handling and statistical methods

At the time of baseline assessment, data is collected on paper forms and then entered into a Microsoft Access database. Data is stored securely at Menzies School of Health Research. In brief, the plan for the analysis is:

Aim 1: descriptive statistics including mean and standard deviation for normally distributed variables, geometric mean and 95% confidence interval for non-normally distributed data, and percentages for categorical variables.

Aim 2: associations of the extent and severity of periodontal disease with measures of vascular health and inflammation from cross-sectional analysis at baseline, using correlation analysis, and multivariable regression modelling adjusted for cardiovascular risk factors.

Aim 3: intention to treat analysis comparing cardiovascular surrogate endpoints between the two randomised groups. Primary outcomes are carotid IMT at 12-months and PWV at both 3- and 12-months. Correlations between the changes from baseline to 3- and 12-months in carotid IMT, PWV and secondary outcomes will be determined.

Appropriate transformation of the data will be performed as required. Crude correlations will be detailed, followed by multivariable modelling. Statistical significance will be inferred at 2*P *≤ 0.05.

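### The 0.80 power claimed for a 10 percent difference in carotid IMT progression is not credible as worded, and the section does not say what the 10 percent is a percentage of

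*Protocol article*

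**What the plan says.** All references are to the protocol article.

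- **Sample size:** 144 participants are said to give "0.80 power to detect a 10 percent difference between groups in carotid IMT progression over 12-months", and the same power for a second effect, "a 10 percent reduction in PWV in the intervention group compared to the control group". The section refers in general terms to studies of Indigenous adults in the Northern Territory and to two cited papers. It gives no mean, SD or difference in mm for IMT, and no mean or SD for PWV.
- **Primary and secondary outcomes:** "The primary outcome measures for purposes of this investigation will be carotid IMT and PWV". Progression is not mentioned.
- **Data handling and statistical methods, Aim 3:** the randomised groups are compared by intention to treat, and "Primary outcomes are carotid IMT at 12-months and PWV at both 3- and 12-months". Change from baseline appears only in the next sentence, for a different purpose: "Correlations between the changes from baseline to 3- and 12-months in carotid IMT, PWV and secondary outcomes will be determined".

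**The concern.** Ten percent of a year's thickening and ten percent of the thickness itself are very different effects, and they are judged against different SDs. The Sample size section attaches the 10 percent to progression, while the analysis section names the 12-month value. A reader cannot tell which effect the 144 was calculated for.

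The literal reading is also demanding. A one-year change is the difference of two ultrasound measurements, so measurement error enters twice, and the true change is small relative to the thickness. Detecting a tenth of that change with 72 people per arm requires very little spread between individuals.

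Carotid IMT is one of two primary outcomes. If the power statement is taken at face value, a null IMT result could be read as evidence against a 10% slowing of progression that the trial may have had little chance of detecting. The same section says that effects of this magnitude are reasonable to expect, which cannot be judged until the base of the percentage is known.

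**Working it through.** **Inputs from the article.** Evaluable total 144, power 0.80 and attrition 45% (Sample size); 1:1 allocation, so 72 per arm (Randomisation); two-sided 0.05 (Data handling and statistical methods). The mean and SD of IMT and of its change are not given.

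**Is 144 a total?** 144 / (1 − 0.45) = 261.8, or 262, against the stated 266. In reverse, 266 × 0.55 = 146.3. The figures agree closely enough to read 144 as the total with 12-month data. The attrition step is not at fault.

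**Can the 0.80 be reproduced?** Not directly, because no SD is stated. The calculation can be inverted.

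*Step 1: detectable difference.* Normal approximation: d = (1.960 + 0.842) × √(2/72) = 0.467 SD. With the noncentral t it is 0.470 SD.

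*Step 2: what 10% of progression requires.* If the difference is 0.10 × mean change, then 0.10 × mean ≥ 0.470 × SD, so SD/mean ≤ 0.10 / 0.470 = 0.213. No outside figure enters this step.

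*Step 3: more generous readings (normal approximation).* A one-sided test at 0.05 raises the limit to 0.24. Taking 144 as the number per arm raises it to 0.30, but this conflicts with the 266.

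*Step 4: power if the ratio is larger (assumed values).* Here d = 0.10 / (SD/mean). Power is from the two-sided noncentral t with 72 per arm; n per arm for 0.80 power is 2 × 2.8016² / d².

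| Assumed SD/mean of 12-month change | d | Power, 72 per arm | n per arm for 0.80 |
|---|---|---|---|
| 0.5 | 0.20 | 0.22 | 393 |
| 1 | 0.10 | 0.09 | 1,570 |
| 2 | 0.05 | 0.06 | 6,280 |

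A second assumed range, in mm, points the same way. With mean progression of 0.01 to 0.05 mm per year, the SD of change would have to be at most about 0.002 to 0.011 mm. In a grid with SDs of change from 0.02 to 0.10 mm, the most favourable pair (mean 0.05, SD 0.02) needs 504 in total and has power 0.32 with 144.

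*Step 5: readings under which 144 suffices.*

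- 10 percent of IMT thickness: the coefficient of variation of the level must be at most about 0.21. With an assumed mean of 0.70 mm and SD of 0.15 mm (ratio 0.214), the total needed is 146, close to the stated 144.
- 10 percentage points of change from baseline: the SD of percent change must be at most 10 / 0.470 = 21 points.

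*Step 6: effect of baseline adjustment.* The 0.47 SD is for an unadjusted comparison. If 12-month IMT is adjusted for baseline with correlation r, the detectable difference is about 0.47 × √(1 − r²) level SDs:

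| Assumed r | Detectable difference (level SDs) | Limit on SD/mean for 10% of the level |
|---|---|---|
| 0.5 | 0.41 | 25% |
| 0.7 | 0.34 | 30% |
| 0.8 | 0.28 | 35% |

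**The case against.** The best defence is that nothing stated is contradicted by arithmetic. The article gives no SD and points to sources not shown here, and the low power figures come from assumed ratios. That stands: the claim cannot be called false. A reader might infer that the trial has almost no ability to detect the stated effect. The documents do not support that, because it depends entirely on the unstated SD and on which meaning of 10 percent was intended. An appeal to normality, under which a ratio of 0.21 would leave almost nobody with a thinner wall after a year, adds little, since the article does not assert normality and allows transformation.

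Second, 10 percent can be read as percentage points or as a share of thickness, and 144 can then be enough. This also stands. It shows that the wording is ambiguous; it does not rescue the literal wording. A 10 percent effect on thickness would also be large: at an assumed 0.70 mm it is 0.07 mm, more than a whole year's progression in the assumed range above.

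Third, under randomisation the expected between-group difference in mm is the same for 12-month IMT as for change from baseline. The abstract speaks of effects on changes, the analysis plan is given only in brief, and baseline adjustment may be left to a fuller document. So the two labels do not by themselves make the analysis wrong. They matter here because they change the base of the 10 percent and the SD it is set against.

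It would also go too far to say that slower progression conflicts with the hypothesis that therapy improves vascular health. Slower thickening than in controls is an improvement.

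Finally, a null result should be judged by its confidence interval rather than by planned power. That is true and limits the harm, but it does not excuse a power statement that cannot be interpreted.

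**Conclusion.** The point holds as a defect in a stated design figure for one of the two primary outcomes. From the article's own inputs, 0.80 power with 72 per arm means 0.47 SD, so a 10% relative difference in progression requires the SD of measured one-year change to be at most about 21% of its mean. That is not credible as worded. It falls short of proof because the SD is not given; power would be 0.22, 0.09 or 0.06 at assumed ratios of 0.5, 1 or 2.

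The 144 fits a 10 percent difference in IMT thickness well, and it is tempting to conclude that the calculation was done for the level and mislabelled. The article does not say so, and a percentage-point reading is also open, so the authors' intent should not be presumed.

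**What to change.** 1. Make Primary and secondary outcomes, Sample size, and Data handling and statistical methods name one IMT quantity: the 12-month value, change from baseline, or percent change.
2. Restate the power for that quantity as an absolute difference in mm, with the assumed mean and SD and their source.
3. Say which SD is meant. For an unadjusted comparison the detectable difference is 0.47 SD. For a baseline-adjusted comparison it is 0.47 × √(1 − r²) level SDs, with r stated. The unadjusted 0.47 SD and 21% limits should not be attached to a baseline-adjusted analysis.
4. Give the PWV mean and SD separately.
5. Unless an SD of change of at most 21% of mean progression can be supported, state that the trial is not powered for a 10% relative change in IMT progression.

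Simply deleting the word progression is not enough, because it would guess at the intended effect and still leave out the mean and SD.

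The cost is a rewritten sample size paragraph and a less favourable IMT power statement. No extra participants are needed.

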### Data handling and statistical methods

At the time of baseline assessment, data is collected on paper forms and then entered into a Microsoft Access database. Data is stored securely at Menzies School of Health Research. In brief, the plan for the analysis is:

Aim 1: descriptive statistics including mean and standard deviation for normally distributed variables, geometric mean and 95% confidence interval for non-normally distributed data, and percentages for categorical variables.

Aim 2: associations of the extent and severity of periodontal disease with measures of vascular health and inflammation from cross-sectional analysis at baseline, using correlation analysis, and multivariable regression modelling adjusted for cardiovascular risk factors.

Aim 3: intention to treat analysis comparing cardiovascular surrogate endpoints between the two randomised groups. Primary outcomes are carotid IMT at 12-months and PWV at both 3- and 12-months. Correlations between the changes from baseline to 3- and 12-months in carotid IMT, PWV and secondary outcomes will be determined.

Appropriate transformation of the data will be performed as required. Crude correlations will be detailed, followed by multivariable modelling. Statistical significance will be inferred at 2*P *≤ 0.05.

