### Randomisation

After screening for periodontal disease, those with moderate or severe periodontal disease are randomised on a 1:1 basis to either the treatment or control group. A computer generated permuted block randomisation sequence is used, stratified by recruitment site (Darwin/Palmerston, Katherine).

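### Three primary comparisons share one unadjusted two-sided 0.05 level with no success rule, so either the error rate or the power differs from what the stated 0.05 and 0.80 suggest

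*Protocol article*

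**What the plan says.** Under Primary and secondary outcomes, the protocol article names two measures without time points: "The primary outcome measures for purposes of this investigation will be carotid IMT and PWV". Under Data handling and statistical methods, Aim 3, these become three comparisons between the randomised groups: "Primary outcomes are carotid IMT at 12-months and PWV at both 3- and 12-months". The same section sets one level for the whole analysis: "Statistical significance will be inferred at" a two-sided P of 0.05 or less.

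Under Sample size, "a sample size of 144 will provide 0.80 power to detect a 10 percent difference between groups in carotid IMT progression over 12-months". The same sentence covers a 10 percent reduction in PWV, also at P < 0.05, and does not say at which visit. Under Aims & hypotheses, Aim 3 has one directional hypothesis, that treatment improves vascular health and inflammatory markers. The article does not rank the primary comparisons, divide the 0.05 among them, or say how many must be significant for that hypothesis to be supported.

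**The concern.** One hypothesis is examined through three primary tests, each at the full 0.05, and the reader is not told what pattern of results would confirm it. If one significant result is enough, the trial has three chances of a false positive, two of them on PWV. A significant 3-month PWV difference with nothing at 12 months could then be presented as support. If more than one result is needed, the 0.80 power describes each outcome separately and not the trial's chance of success. Because the sample size is also built on the full 0.05 for each outcome, an adjustment added later would no longer match the stated power.

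**Working it through.** **Inputs from the protocol article.** Three primary comparisons and a two-sided 0.05 level (Data handling and statistical methods); 144 evaluable, power 0.80, 45 percent attrition and 266 at baseline (Sample size); 1:1 allocation (Randomisation), so 72 per arm.

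**Inputs assumed.** The article gives no correlations between the three test statistics, so a range is used. The 3-month PWV test is given the same 72 per arm as the 12-month tests. Power uses the normal approximation.

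**1. The plan's own figures.** Baseline number: 144 / (1 − 0.45) = 261.8, so 262 against the stated 266, which is close enough. The 144 cannot be rebuilt because no SD is given. It implies a standardised effect of (1.960 + 0.842) × √(2/72) = 0.467, which for a 10 percent difference means an SD of 0.10/0.467, about 21 percent of the reference value.

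**2. Any one of three suffices.** Under independence, 1 − 0.95³ = 0.143. For correlated tests, three two-sided z-tests were simulated under no effect, with at least 2 million draws per setting. The false-benefit column counts only errors in favour of treatment; under independence it is 1 − 0.975³ = 0.073.

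| Correlation, PWV 3 vs 12 months | Correlation, PWV vs IMT | At least one false result, two-sided | At least one false benefit |
|---|---|---|---|
| 0 | 0 | 14.3% | 7.3% |
| 0.5 | 0.2 | 13.4% | 6.8% |
| 0.6 | 0.2 | 13.1% | 6.6% |
| 0.7 | 0.3 | 12.6% | 6.3% |
| 0.8 | 0.3 | 12.1% | 6.1% |
| 0.9 | 0.5 | 10.9% | 5.4% |

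If IMT is independent of PWV and the two PWV tests are perfectly correlated, the two-sided rate is that of two tests: 1 − 0.95² = 9.75%.

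**3. Both outcomes must succeed at 12 months.** Each test has power 0.80. Joint power is 0.80 × 0.80 = 0.64 at correlation 0, and about 0.68 at correlation 0.4.

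**4. Power under a stated rule, 144 evaluable.**
- At 0.05/3 = 0.0167: Φ(2.802 − 2.394) = Φ(0.408), about 0.65-0.66.
- Under full Holm, with all three effects as planned, simulation at the four middle correlation pairs in the table gives about 0.73-0.75 per comparison, because later steps are less strict.
- Under a fixed sequence, the first comparison stays at 0.05 and keeps 0.80.

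**5. Baseline adjustment at 0.05/3.** The gain depends on what the planning SD described.

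| Baseline correlation r | SD was for final values (variance × (1 − r²)) | SD was for change (variance × (1 + r)/2) |
|---|---|---|
| 0.5 | 0.80 | 0.80 |
| 0.7 | 0.94 | 0.74 |

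The sample size section describes the IMT effect as a difference in progression, which points towards change, but gives no SD that would settle it.

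**The case against.** The strongest reply is that this is a condensed article whose analysis section calls itself brief, and that multiplicity rules are commonly left to a statistical analysis plan, which is not shown. Naming several primary outcomes with a conventional 0.05 is not a declaration that nothing will be adjusted. That would answer a complaint about silence alone. It does not fully answer this one, because the article fixes the three comparisons and the single level, and powers both outcomes at that level. An adjustment made elsewhere would depart from the published level and make the 0.80 wrong.

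A reader might infer that the trial's true error rate is 12-14% against a promised 5%. The article does not support that. It never claims family-wise control, 0.05 is correct for each test, and it does not say that one significant result is enough. The 14.3% is conditional on that rule and on independence; the lower values rest on assumed correlations.

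A reader might also infer that baseline adjustment makes the correction free. That does not follow: if the planning SD was already for change, stronger baseline correlation recovers less, as step 5 shows.

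It is also fair to say that all three comparisons are disclosed in advance, so readers could apply their own correction. That limits the harm, but does not tell them what the trial set out to show.

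**Conclusion.** The concern holds as an unstated decision rule with consequences on either reading. If any one result counts, which the text permits, the two-sided family-wise error is 14.3% under independence and about 11-13% at the positive correlations tried, more than twice 0.05 in each case. False benefit is about 5-7% against 2.5%. If both outcomes must succeed at 12 months, type I error is not inflated, but joint power is about 0.64-0.68 for correlations of 0 to 0.4. Neither reading combines a 5% error rate with 0.80 power for the Aim 3 conclusion. The calculations take the planned effect and 72 evaluable per arm as given.

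**What to change.** Add one sentence to the Aim 3 analysis plan before any unblinded analysis. Either of these would do:

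- The three primary comparisons are tested with the Holm procedure at a family-wise two-sided 0.05.
- The three primary comparisons are tested at two-sided 0.05 in a pre-specified fixed sequence, stopping at the first that is not significant. The sponsor should choose the first comparison and justify it. Blinding bears on that choice: the article says the PWV observer will not be blinded to participant characteristics, whereas IMT images are read blind to group and visit.

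Then restate power in the sample size section under the chosen rule, and say which PWV visit it refers to and whether the planning SD was for final values or for change.

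The cost is power, not drafting. With 144 evaluable, Holm gives about 0.65 at its strictest step and about 0.73-0.75 per comparison overall if all effects are as planned. A fixed sequence keeps 0.80 for the first comparison, but later ones can be claimed only if those before them succeed. Holding 0.80 for each comparison at 0.05/3 would need 144 × (3.236/2.802)² = about 192 evaluable (194 in whole arms on the re-derived effect), or 194/0.55 = about 353 at baseline instead of 266. Baseline adjustment may recover part of the loss, but should be credited only once the source of the SD is known.

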## Discussion

The PerioCardio study will provide answers to three key questions: (1) the extent of severity of cardiovascular surrogate endpoints in an Indigenous adult population with periodontal disease; (2) whether the extent and severity of periodontal disease correlates with measures of vascular health and inflammation in Indigenous Australian adults and; (3) whether intense periodontal therapy improves these markers of vascular health and inflammation.

Furthermore the PerioCardio study will be the first investigation examining the effectiveness of periodontal therapy in changing cardiovascular surrogate endpoint levels in an Indigenous Australian population, and the first investigation to monitor changes in cardiovascular surrogate endpoints following periodontal intervention at both 3- and 12-months.

As such, the PerioCardio study will have significance for policy and planning by providing evidence of the relationship between periodontal disease, periodontal therapy, and cardiovascular disease among Indigenous Australian adults with periodontal disease, and the effectiveness of an intervention aimed at improving periodontal and cardiovascular health in an Indigenous population. Efforts to understand and improve Indigenous oral health and cardiovascular risk may serve as an important means of reducing the gap between Indigenous and non-Indigenous health in Australia.

The findings may help raise the profile of the role of periodontal disease in cardiovascular health; thus increasing the knowledge base of those working intimately with patients with cardiovascular disease. Ultimately it is hoped that the findings might encourage greater dialogue between oral health and medical professionals so that periodontal treatment might become a routine part of care in the treatment of cardiovascular disease among Indigenous as well as non-Indigenous populations.
